#### Details of Inclusion Criteria

Based on previous work aiming to prevent major depression, we will initially select at-risk mothers

using two criteria: 1) a recent history of depression, or 2) current subsyndromal depressive symptomatology. This screening component (a 5 question screener) will be embedded within Head Start caseworkers' Strength and Needs Assessment of Head Start families. The primary purpose of this is to screen people *into* the study.

Mothers who are positive on this initial recruitment screen will be called by research staff and will be asked permission for a second screen to determine if they are currently (past 2 weeks) in a Major Depressive Episode using the M.I.N.I. MDE Module. The primary purpose of this is to screen people *out* of the study.

Only mothers who are both positive on the 5 question recruitment screen AND who are MDE negative in the past 2 weeks will engage in formal written informed consent.

Immediately after the written informed consent process (described later), we will use the MacArthur Competence Assessment Tool for Clinical Research (MacCAT-CR) to determine the potential subject's capacity to consent to research. This screening tool will screen out any mothers who are psychotic, or impaired in their capacity to participate in a research study. The MacCAT-CR thus serves the dual purpose of confirming one's ability to provide informed consent and screening out thought-disordered individuals from a study that is not appropriate for them.

Next, we will use the MacArthur Suicide Screening Questions to assess suicidal ideation at low, intermediate or high risk. We will only accept mothers into the study who are at low or intermediate risk for suicide. This means that either mothers with no current thoughts or with current thoughts but no plans of suicide will be eligible for participation. The reason for this exclusion criterion is participant safety. Our plans to manage a crisis brought on by the expression of suicidal ideation are also detailed in our attached protocols.

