### Design

At present, all Head Start mothers are given social work and case management services and education by the Head Start team regarding the importance of physical and mental health care. Mothers are screened for mental health needs during their "strength and needs assessment" by the case management staff and given referrals to care when necessary. However, there is no systematic depression prevention strategy, and there is no tested, evidence-supported mechanism to get depressed parents quality mental health care.

Study design. Parallel group, RCT involving mothers whose children attend Head Start - a comprehensive preschool program for low-income children birth to 5. Eligible mothers will be randomized to receive PSE or standard of care at Head Start. Both groups will be followed for 12 months.

Participants. 230 Head Start mothers (115, PSE; 115, control) will be enrolled in the at-risk stratum.

Randomization. The unit of randomization will be the mother. Investigators and data collectors will be blinded to study allocation. We could have chosen a number of study designs, including cluster randomization by caseworker or Head Start center. Cluster randomization, however, has its own set of methodologic shortcomings, notably post-randomization selection bias. Because we also expect high intra-class correlation among families within the same Head Start center, a cluster design on this basis would create unrealistic sample size requirements. Conversely, the only substantial drawback of a parallel design would be a conservative bias in favor of the control arm due to intervention spillover. However, because control subjects will not have access to trained educators, we anticipate such effects to be minimal. Randomization will occur independently within each Head Start site, within strata defined by the presence or absence of depression history. We will randomize 1:1 within randomly varying blocks of 2 and 4.

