8. Outcome assessments: Each subject will have a 12-month follow up period, during which blinded research assistants will assess outcome measures. Follow-up data collection will begin 2 months after baseline because a full, 6-session course of PSE typically lasts 6-8 weeks. To limit attrition, we will employ a combination of monetary incentives and postcard reminders. Through these strategies, approved by the BUMC IRB in our pilot work, we have been able to maintain follow up rates > 85% across all relevant ongoing studies (there is a separate section on participant compensation in the protocol manual).

Baseline, 6-month, and 12-month assessments will take place in person with a staff RA. We will administer the QIDS and mental health service use questions on a bimonthly basis throughout the study period, and this will be done by telephone by a staff RA.

The 6-month interview will comprise the following valid and reliable scales:

- a. Perceived Stress Scale
- b. M.I.N.I. Depression Module
- c. QIDS
- d. Mental Health Service Use questions (adapted from Collaborative Psychiatric Epidemiology Surveys)
- e. Social functioning (Social Adjustment Scale-Self Report)
- f. Parenting Stress Index
- g. Problem Solving Questions (Social Problem Solving Inventory)
- h. Coping Questions (Brief COPE)
- i. Pearlin Mastery Scale
- j. Behavioral Activation for Depression Scale
- k. Rosenberg Self-Esteem Scale

The 12-month interview will comprise the following valid and reliable scales:

- a. Perceived Stress Scale
- b. M.I.N.I. Depression Module
- c. QIDS
- d. Mental Health Service Use questions (adapted from Collaborative Psychiatric Epidemiology Surveys)
- e. Social functioning (Social Adjustment Scale-Self Report)
- f. Problem Solving Questions (Social Problem Solving Inventory)
- g. Coping Questions (Brief COPE)
- h. Pearlin Mastery Scale
- i. Behavioral Activation for Depression Scale
- j. Rosenberg Self-Esteem Scale
- k. Recent Life Changes Questionnaire

- I. Mood, anxiety and alcohol and other substance use, modules of the SCID

RA's will be trained not to leave telephone messages, and to introduce themselves as from "BMC" so as to ensure confidentiality.

9. At 6-months post randomization, parents and Head Start teachers will be asked to fill out the Social Skills Rating System (SSRS) with reference to all 3-5 year-old Head Start children of enrolled parents.
10. We will assess rate of absenteeism from Head Start for children of mothers who are in our study.

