##### Major Depressive Episode Screen

Mothers meeting either of these eligibility criteria will be offered to meet with a research assistant, who

will conduct a second verbal consent to screen for current MDE using the MINI MDE module.

Once the MINI is performed, research staff will obtain written consent, administer the in-person baseline survey, and randomly assign study allocation only if mothers meet the inclusion and exclusion criteria as outlined above (The baseline instrument is provided in the study binder).

Two important factors require us to temporarily record names of the potential subjects screened with this instrument:

- Screening for depression is part of normal Head Start practice through their "strength and needs assessment;" this initial screener will be done by Head Start staff. Therefore, Head Start sites have the option of using the PHQ2 AS BOTH A STUDY SCREENING INSTRUMENT AND A CLINICAL TOOL USED BY HEAD START STAFF. In order that it fulfill the latter purpose, an identifier is necessary - not for study personnel, but rather for Head Start personnel.
- Because Head Start staff will be conducting these initial screens (not study personnel), it is necessary that they be reviewed by study staff to most accurately determine ultimate study eligibility. We thus plan that study personnel review the screening results with Head Start staff.

We will therefore write the verbal consent form to explicitly inform potential subjects that this screening form will be reviewed one time by study personnel and that the information on the screen will not be recorded for any study purpose aside from what is mentioned above.

Furthermore, to safeguard confidentiality, the 'name' field will be replaced by a temporary study code. Head Start staff will keep the cross-walk between temporary codes and actual names in a separate location. The screening form, code, and cross-walk will all be destroyed as soon as study eligibility is determined.

A script for the initial case worker approach is will be kept in the study binder and provided to the IRB. We will also provide Head Start sites with study pamphlets to help introduce the research study in Head Start. These pamphlets will also be kept in the study binder and supplied to the IRB.

Recruitment Materials will all be available in the study binder.

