#### **Consent Procedures**

RAs working for [name] will obtain consent and describe the informed consent process prior to definitively determining eligibility. Potential subjects will have as long as they wish to consider participating.

Our detailed consent and eligibility determination processes are as follows:

1. Head Start caseworkers will obtain verbal consent to screen clients for eligibility, as detailed above. We do this so mothers who are NOT at risk for depression-and therefore not appropriate for the study-will not be unnecessarily inconvenienced. This verbal consent and screen will occur in person or on the telephone. The latter mechanism is necessary because the mothers are frequently in phone contact with their Head Start caseworkers, but may not see them in person more than every month; and although the mothers will often come to Head Start to pick up their children, they usually do not see their caseworkers during this time (the verbal consent form is provided in the study binder). This process will be conducted by Head Start caseworkers.
2. Once caseworkers refer mothers who have screened positive for symptoms and/or a history, staff RA's will conduct a second verbal consent and screen additionally to see if the mother is currently in a Major Depressive Episode.
3. If mothers are eligible on recruitment screen AND are not currently in a Major Depressive Episode, written informed consent will be obtained by staff RAs. This will occur in person. The RA script for informed consent is provided in the study binder and will be supplied to the IRB. Research assistants will be trained to explain that written informed consent is required prior to eligibility screening due to the type of information collected. This is particularly important because if potential participants screen positive for suicidality, the study's crisis management protocol will be activated (available in binder and provided to the IRB).
4. Mothers will be explained during consent procedures that they will be randomized into either the supplement (H-31999) or the prevention trial (this protocol). If they are randomized into the prevention trial (this protocol), they will be explained that they will randomized a second time into the intervention or control group.

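### The staff who consent and interview mothers are also said to assign the arm, against the stated blinding; with blocks of only 2 and 4, allocation could then be partly predictable

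*Protocol*

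**What the plan says.** **Allocation scheme (Protocol, Design).** "Randomization will occur independently within each Head Start site, within strata defined by the presence or absence of depression history". Within those strata, "We will randomize 1:1 within randomly varying blocks of 2 and 4".

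**Blinding (Protocol, Design and Procedure).** "Investigators and data collectors will be blinded to study allocation". Procedure item 8 describes the 12-month follow-up as a period "during which blinded research assistants will assess outcome measures".

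**Who enrols and who allocates (Protocol, Major Depressive Episode Screen and Consent Procedures).** "research staff will obtain written consent, administer the in-person baseline survey, and randomly assign study allocation only if mothers meet the inclusion and exclusion criteria". Consent Procedures identifies the consenting staff: "written informed consent will be obtained by staff RAs".

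**Steps just before allocation.** Under Procedure, research assistants book the second screening visit. Consent Procedures has them run the screen for a current depressive episode. After written consent come the MacCAT-CR and the suicide-risk grading: "we will use the MacArthur Suicide Screening Questions to assess suicidal ideation at low, intermediate or high risk". Either can exclude a mother. The baseline survey follows, then randomisation.

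**Contact between teams.** The Data Safety Monitoring Plan has investigators, educators and research assistants meeting weekly to go over cases. The Study Summary says the linked pilot in depressed mothers shares staff with this trial for both enrolment and outcome assessment.

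**The concern.** Mothers and educators necessarily know who receives PSE. The blinding therefore has to protect the research assistants, and it matters at two moments: when they assess outcomes, and earlier, when they decide whom to book, in what order, and whether a mother passes the exclusion screens. This point is about the earlier moment.

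A person who assigns the arm learns the arm. If those who consent and interview also assign, they build up a record of earlier allocations at their site. The weekly case meeting is a second possible source. Short blocks make such a record informative about the next assignment. Someone who can guess the next arm may, without intending to, defer, hurry or exclude a mother according to how she seems likely to fare.

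The three primary outcomes (SPSI-R score, rate of QIDS elevations, mean QIDS over time) all rest on the mother's own answers. Intention-to-treat analysis compares the arms as randomised, so it does not undo selection that took place before randomisation.

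**Working it through.** The Protocol gives no predictability figure, so there is none to reproduce.

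**Inputs from the Protocol:** 1:1 allocation; block sizes 2 and 4; two history strata per site; 230 randomised; 100 analysable per group; detectable SPSI-R effect 0.4 SD.

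**Assumptions:** block sizes equally likely; the guesser knows every earlier allocation in the stratum but not the current block size. The number of sites is not stated, so 3 to 20 are tried. The strength of selection is not stated either.

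**1. Guess rate in complete blocks.** Guess the arm that is behind in the stratum, and toss a coin at a tie. Every block ends balanced, so varying the size does not defeat this strategy. Expected correct guesses in a block of size 2k are k + 2^(2k−1)/C(2k,k) − 1/2.
- Block of 2: 1 + 2/2 − 0.5 = 1.5, and 1.5/2 = 75.0%.
- Block of 4: 2 + 8/6 − 0.5 = 2.833, and 2.833/4 = 70.8%.
- Equal mix: (1.5 + 2.833)/6 = 72.2%.

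**2. Guess rate in finite strata (simulated).** With 230 mothers over 3 to 20 sites, the rate is 69% to 72%. With 5 sites (10 strata of 23) it is 71.2%. A Bayes-optimal guesser gives the same: 71.6% in strata of 12 and 71.2% in strata of 23.

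**3. Certain assignments.** A two-mother lead can arise only when a block of 4 opens with two identical assignments (probability 1/3), and the next two are then forced. Per one block of each size, that is (1/3 × 2)/6 = 11% in complete blocks, and about 10% in finite strata by simulation.

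**4. Effect on the comparison.** Suppose mothers enrolled on a PSE guess are d SD better and those on a control guess d SD worse. With guess rate p, the spurious difference is 2d(2p − 1), the z-shift is that times √(100/2), and the two-sided type I error is P(|Z + shift| > 1.96).

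| p | d (assumed) | Spurious difference | z-shift | Type I error |
|---|---|---|---|---|
| 0.50 | any | 0 | 0 | 5% |
| 0.71 | 0.1 | 0.2 × 0.42 = 0.084 SD | 0.59 | about 9% |
| 0.71 | 0.2 | 0.4 × 0.42 = 0.168 SD | 1.19 | about 22% |

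Against the planned 0.4 SD, these differences are 0.084/0.4 = 21% and 0.168/0.4 = 42%.

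**5. Larger blocks.** With sizes 4, 6 and 8 and the same full knowledge, accuracy is 66% to 67% and about 2% of assignments are certain. At p = 0.667 and d = 0.1, the spurious difference is 0.2 × 0.334 = 0.067 SD and the type I error about 7.6%.

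**6. Cost in balance, 10 strata of 23.** With blocks of 2 and 4, an odd-sized stratum always ends exactly one mother out of balance, so the SD of the overall arm-size difference is √10 = 3.16. With 4, 6 and 8 it is about 3.6 by simulation.

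**The case against.** The best counterargument is that the exposure is inferred. Design and Procedure state the blinding outright. The sentence on assigning allocation sits in a recruitment section and mainly sets the order of steps. The Protocol uses the term research staff loosely: Procedure item 6 applies it to the PSE educators too. So one person need not perform all three tasks, and nothing says that recruiters see past assignments. This stands in part. The text is a conflict to be resolved, not proof of exposure. Calling the trial simply open, or saying that recruiters see earlier allocations, would go beyond it.

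Other limits also stand:
- The 71% is a ceiling for someone with full knowledge of the stratum. A reader might take it as the rate recruiters will achieve, which the Protocol does not support.
- Caseworkers do the first screen, the exclusion screens are named instruments, and consented mothers are first randomised between the supplement and this trial. These steps narrow the room for steering without closing it, because research assistants still book the visits, run the depressive-episode screen and take consent.
- Reordering needs two or more mothers waiting in the same stratum, and no such figure is given.
- Data Analysis allows regression adjustment for SPSI-R if baseline differences are significant. That is a partial safeguard, for measured differences only.
- Larger blocks alone change little. With working concealment, blocks of 2 and 4 do little harm.

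The objection does not remove the conflict itself, nor the weekly meeting that brings masked assistants together with educators who know the arm.

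**Conclusion.** The point holds as a contradiction with a possible consequence. As written, the recruitment section gives allocation to the staff who consent and interview, while Design and Procedure call data collectors blinded. If enrolling staff did learn earlier allocations, blocks of 2 and 4 in every site-by-history stratum would let them guess up to about 71% of next assignments (69% to 72% over 3 to 20 sites) and know about 10% with certainty. If masking works, the rate is 50%.

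A reader might conclude that the primary comparisons are biased. The Protocol does not support that: bias is possible, not shown. The 0.08 SD and 9%, or 0.17 SD and 22%, rest on assumed selection of 0.1 or 0.2 SD acting at every guess. The allocation procedure should nevertheless be corrected, because the change is cheap and the analysis could not repair such bias afterwards. Block size is the lesser cause.

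**What to change.** **Main change (Major Depressive Episode Screen section).** Take allocation out of the duties of the staff who consent and interview. State that:
- an existing team member who neither recruits nor assesses holds the list;
- each assignment is released only once eligibility and the baseline survey are complete, and goes to staff other than the enrolling or assessing research assistants;
- someone other than those assistants tells mothers in both arms, controls included;
- enrolling assistants stay masked to earlier allocations, including in the weekly meetings, where cases would have to be discussed without revealing the arm or in separate sessions.

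If the statistician is to hold the list, the text should say how this fits with that person's part in weekly data monitoring.

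**Secondary change (Design).** Use larger randomly varying blocks, for example 4, 6 and 8, in the same strata, and keep the sizes in a restricted document. Under full knowledge this lowers the guess rate only from about 71% to 67%; the clearer gain is in certain assignments, from about 10% to 2%.

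**Cost.** A wording amendment and a regenerated list, with no extra staff. Balance loosens slightly: the SD of the overall arm-size difference rises from 3.16 to about 3.6 mothers under the assumed 10 strata of 23, which is negligible for power with 230 randomised.

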### Procedure

1. Boston's ABCD Head Start will obtain a Federalwide Assurance (FWA00016040), on which it will designate the BUMC IRB. All personnel at ABCD Head Start deemed to be engaged in research will take the online NCI course in human subjects protections, and certificates will be emailed to the BUMC IRB. Additionally, such personnel will receive project-specific training directly from [name] (PI) and [name] (co-I). We currently have an IRB approved IAA with ABCD Head Start.
2. The trial will be registered on clinical trials.gov prior to enrolling participants.
3. The PI and study coordinator will update NIMH's RMR (Recruitment Milestone Report) per NIMH's schedule.
4. Participants: 230 at-risk Head Start mothers will be enrolled according to the eligibility criteria indicated in previous section.

5. Procedures pre-written informed consent

- a. Verbal Consent 1 and Recruitment Screen: Verbal consent will be used prior to screening for eligibility with a temporary study code; Head Start caseworkers will conduct this initial round of screening and determine with study staff IRB-compliant modes of communication to make staff aware of mothers with positive screens. Only eligible subjects' names and telephone numbers will be recorded during screening, in addition to the screening results.
  - b. Verbal Consent 2 and MDE Screen: Research assistants will set up appointments with eligible mothers (those positive in recruitment screen) to conduct a second verbal consent and screen to determine if eligible mother is currently in a Major Depressive Episode.
  - c. Only eligible mothers (positive on recruitment screen and negative on MDE screen) will be offered written informed consent.
  - d. For those individuals who refuse screening, are not eligible or opt not to participate, we will record only their temporary study code on the recruitment screen. We will submit this list of temporary study codes to Head Start personnel for two reasons: 1) to avoid inadvertent re-approaching; and 2) so that Head Start can supply the study team with an anonymized demographic description of this population with a de-identified list of demographic characteristics, (Attached in the study binder). Specific variables will include only those that Head Start keeps for programmatic reasons (the equivalent of existing clinical data): age, language spoken, place of birth, race, ethnicity, education, work status, marital status, household type (single or double-headed household), number of people in household, living situation, income, health insurance status, type of government assistance.
4. Written Informed Consent: After the two screens are administered and the potential subject is found to be eligible, the subject will be enrolled (if willing) into either the RCT or into a small supplemental pilot study of 'PSE Lite.' Immediately following the signing of the consent form, the following will happen:
- a. Subjects will be administered either the MacCAT-CR immediately after the consent form in order to ensure that subjects with limited cognitive capacities and/or major mental illness, including psychosis, are safeguarded from being in the study.
  - b. Subjects will be screened for suicidal ideation in order to safeguard subjects with high suicidal ideation. Our crisis protocols will be activated as necessary (Crisis Management Plan, Domestic Violence Protocol, Referral of Clients with Trauma or Substance Use – each protocol is provided in the study binder).
5. Once participants have completed the safeguards outlined in above, we will collect the following data from all mothers enrolled in the study *prior to* randomization. The interviews will be completed in private rooms at the Head Start center, or in subjects' homes (subjects' choice). The Baseline Survey will comprise the following valid and reliable scales:
- a. Children with Special Health Care Needs Screener

- b. Perceived Stress Scale
  - c. M.I.N.I. Depression Module (current or recurrent Major Depressive Episode (We will use the data from the second verbal screen for this. We have added this permission to the written consent form.))
  - d. Quick Inventory of Depressive Symptoms. Beck Anxiety Inventory
  - e. Mental Health Service Use questions (adapted from Collaborative Psychiatric Epidemiology Surveys)
  - f. Medical Outcomes Study – Social Support Survey
  - g. Social functioning (Social Adjustment Scale-Self Report)
  - h. Problem Solving Questions (Social Problem Solving Inventory)
  - i. Substance Use (CAGE-AID and AUDIT)
  - j. Coping Questions (Brief COPE)
  - k. Rosenberg Self-Esteem Scale
  - l. Behavioral Activation for Depression Scale
  - m. Pearlin Mastery Scale
  - n. Stressful Life Events Questionnaire
  - o. Modified PTSD Symptom Scale
  - p. Demographics
  - q. Behavioral Activation Score
6. If randomized to the PSE group, we will employ a team of 4 to 6 research staff (at any given time) to serve as interventionists (referred to as educators or providers). The educators will deliver up to 6 PSE sessions with their clients, each session expected to take 30-45 minutes. Sessions will be delivered either weekly or biweekly, according to the wishes of the subject – with a full course of PSE expected to last 8 weeks. Sessions will be delivered at a location of the subject's choosing. In addition to PSE, intervention subjects will be periodically screened with the PHQ-9 as part of 3 out of the 6 PSE sessions. A score of 15 or greater will require the educator to refer the mother to more definitive mental health care. These referrals will be "activated," meaning that the PSE educators will employ motivational interviewing techniques to help the mothers follow through with the referrals. Lastly, educators will phone their clients monthly to conduct brief "booster session" check-in's.
- Request to audiotape a randomly selected PSE will be embedded in the initial consent form; this will be offered to all subjects for the sake of monitoring treatment fidelity. It will be made clear that subjects can refuse audiotaping but still partake in the rest of the study.
7. Control group: We have chosen our control group to best approximate "usual care" in Head Start. Thus, families will be followed by their Head Start caseworkers, and screened periodically for depression when deemed necessary by Head Start staff, per their usual routine. Referrals will be made

according to criteria specified in the grant application.

8. Outcome assessments: Each subject will have a 12-month follow up period, during which blinded research assistants will assess outcome measures. Follow-up data collection will begin 2 months after baseline because a full, 6-session course of PSE typically lasts 6-8 weeks. To limit attrition, we will employ a combination of monetary incentives and postcard reminders. Through these strategies, approved by the BUMC IRB in our pilot work, we have been able to maintain follow up rates > 85% across all relevant ongoing studies (there is a separate section on participant compensation in the protocol manual).

Baseline, 6-month, and 12-month assessments will take place in person with a staff RA. We will administer the QIDS and mental health service use questions on a bimonthly basis throughout the study period, and this will be done by telephone by a staff RA.

The 6-month interview will comprise the following valid and reliable scales:

- a. Perceived Stress Scale
- b. M.I.N.I. Depression Module
- c. QIDS
- d. Mental Health Service Use questions (adapted from Collaborative Psychiatric Epidemiology Surveys)
- e. Social functioning (Social Adjustment Scale-Self Report)
- f. Parenting Stress Index
- g. Problem Solving Questions (Social Problem Solving Inventory)
- h. Coping Questions (Brief COPE)
- i. Pearlin Mastery Scale
- j. Behavioral Activation for Depression Scale
- k. Rosenberg Self-Esteem Scale

The 12-month interview will comprise the following valid and reliable scales:

- a. Perceived Stress Scale
- b. M.I.N.I. Depression Module
- c. QIDS
- d. Mental Health Service Use questions (adapted from Collaborative Psychiatric Epidemiology Surveys)
- e. Social functioning (Social Adjustment Scale-Self Report)
- f. Problem Solving Questions (Social Problem Solving Inventory)
- g. Coping Questions (Brief COPE)
- h. Pearlin Mastery Scale
- i. Behavioral Activation for Depression Scale
- j. Rosenberg Self-Esteem Scale
- k. Recent Life Changes Questionnaire

- I. Mood, anxiety and alcohol and other substance use, modules of the SCID

RA's will be trained not to leave telephone messages, and to introduce themselves as from "BMC" so as to ensure confidentiality.

9. At 6-months post randomization, parents and Head Start teachers will be asked to fill out the Social Skills Rating System (SSRS) with reference to all 3-5 year-old Head Start children of enrolled parents.
10. We will assess rate of absenteeism from Head Start for children of mothers who are in our study.
11. [name] or [name] will meet weekly with all educators for a supervision meeting. During this meeting, all cases will be discussed. In addition to this, [name] - a board certified psychiatrist from Children's Hospital Boston - will be available for back up and for the rare, but possible, mental health emergency.

